### Specific aims

#### Aim 1 (primary analyses)

Compare the effects of the combined cognitive behavior and physical therapy (CBPT) intervention condition versus a sham control condition on balance confidence and performance-based measures of balance and functional mobility in lower limb prosthesis users.
*Hypothesis 1a*: Participants receiving CBPT intervention will demonstrate improvements in balance confidence over time compared to participants in the control condition.*Hypothesis 1b*: Performance-based measures of balance will improve after CBPT intervention.*Hypothesis 1c*: Performance-based measures of functional ability will improve after CBPT.

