It is expected that 70 participants will be recruited in order to obtain a total of 60 eligible participants (30 intervention and 30 control participants), assuming a 15% drop-out rate. Using G*Power 3.1, a sensitivity analysis (with regard to Hypothesis 1a) was conducted, specifying a power of 0.80, an alpha of 0.05, and an average correlation of observations of 0.50. According to the analysis, with 30 participants in each group we will be able to detect a small to medium effect (f = 0.152) of intervention on ABC score over time with this design, which is consistent with the size of effect observed for older adults [10, 11]. We will have similar power for all hypotheses in Aim 2, which use the same analysis as Hypothesis 1a; we will have power to detect a medium effect size (d = 0.46) for Hypothesis 1b and a correlation of r ≥ 0.42 for Hypothesis 3.

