### Analysis plan

To test Hypothesis 1a we plan to use a 2 (group) × 4 (time point) mixed ANOVA to examine if there are significant differences in changes in ABC scores between the groups (i.e., an interaction effect), accounting for any missing data. In the event of a significant interaction, a post-hoc paired *t*-test will be used to compare ABC scale in the intervention group at 0 and 25 weeks and independent samples *t*-test to compare ABC scale between groups at 25 weeks.

To test Hypotheses 1b and 1c we will use a paired *t*-test to compare BBS scores and L-test times pre- and post-intervention. H1b and c do not compare time-related changes in performance between groups as they are only intended to assess the immediate effects of intervention.

The same analyses from Hypothesis 1a will be used to test all hypotheses in Aim 2. For Hypothesis 2a, a group × time interaction on self-reported community participation measures (CRIS, FAI, SF36 scales) and objective measures from the activity monitors will be tested. A false-discovery rate correction method will be used to minimize the likelihood of type I errors. For Hypothesis 2b, an interaction on the QoL score will be tested. In the event that H2a is not supported, alternative measures to assess integration will be considered.

To test Hypothesis 3 changes in ABC scores (0 weeks to 25 weeks) will be correlated with changes in self-reported and objective measures of community participation. A false-discovery rate correction method will be administered to minimize the likelihood of type I errors. In the unlikely event that Hypotheses 1a and 2a are not supported, this would not exclude the possibility of an association between subject-specific changes in confidence and participation. In such a case, a significant correlation would suggest that improving balance confidence can increase participation, but for optimum effectiveness of the intervention, one should only train individuals who are most likely to respond to the intervention (show large increase in ABC scores). As an initial step to identify commonality among “responders” we would employ a suite of supervised learning techniques (e.g., cluster and canonical correlation analysis) to explore multidimensional relationships among responses to individual items on the ABC, BBS, CRIS, and SF36.

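### The detectable effects for H1b (d = 0.46) and H3 (r ≥ 0.42) fit only undeclared one-sided tests, and the power statements for H2a and H3 leave out the planned false-discovery-rate correction

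*Protocol article*

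**What the plan says.** The sensitivity analysis in the Participants section is described as "specifying a power of 0.80, an alpha of 0.05, and an average correlation of observations of 0.50". The planned size is "a total of 60 eligible participants (30 intervention and 30 control participants), assuming a 15% drop-out rate". For H1a it reports: "with 30 participants in each group we will be able to detect a small to medium effect (f = 0.152"). It then extends the claim to Aim 2: "We will have similar power for all hypotheses in Aim 2, which use the same analysis as Hypothesis 1a". For the remaining hypotheses it states "power to detect a medium effect size (d = 0.46) for Hypothesis 1b and a correlation of r ≥ 0.42 for Hypothesis 3". Sidedness is not mentioned.

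The Analysis plan gives the tests: "To test Hypotheses 1b and 1c we will use a paired" *t*-test of pre- against post-intervention values, and for H3 a correlation of change scores. H1b reads "Performance-based measures of balance will improve after CBPT intervention", and H3 is confined to the intervention condition and predicts a direct correlation. Both therefore rest on 30 people. For H2a the Analysis plan adds: "A false-discovery rate correction method will be used to minimize the likelihood of type I errors". It repeats the correction for H3. The H2a correction is stated before H2b is introduced, and H2b is tested on a single quality-of-life score.

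**The concern.** Two things do not fit together.

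First, the paragraph gives one alpha, 0.05, and opens with a non-directional F test. A reader would carry that convention through to d and r. On ordinary two-sided tests neither figure follows from 30 people.

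Second, the claim for Aim 2 rests on the analysis being the same as for H1a. For H2a it is not quite the same, because an FDR correction sits on top of the F test. The H3 figure has the same gap.

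H1b belongs to the aim labelled primary. The Analysis plan also attaches consequences to H2a and H3. If H2a is not supported, alternative integration measures will be considered. H3 is to be interpreted even if H1a and H2a fail. Anyone weighing a null result against a stated 80% power would give it more weight than the design supports.

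**Working it through.** **Inputs from the article.** Power 0.80, alpha 0.05, correlation between observations 0.50, four time points, 30 per arm (N = 60). H1b and H3 use n = 30.

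**1. H1a, to confirm the method.** Within-between interaction F with df 3 and 174, λ = f² × N × 4 / (1 − 0.50) = 480 f². At f = 0.152, λ = 11.09 and power is 79.8%. The f for exactly 80% is 0.1524, so the stated 0.152 reproduces.

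**2. H1b, paired *t*.** Noncentral *t*, df = 29, noncentrality d√n = 0.46 × √30 = 2.52.

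| | Critical t | Power at d = 0.46 | d at 80% power |
|---|---|---|---|
| One-sided | 1.699 | 79.3% | 0.465 |
| Two-sided | 2.045 | 68.3% | 0.529 |

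The stated 0.46 is the one-sided value.

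**3. H3, correlation.** In the point-biserial model the noncentrality is √(n r² / (1 − r²)) = √(30 × 0.1764 / 0.8236) = 2.53, with df = 28. The bivariate-normal model is the natural one for two continuous change scores.

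| | Point-biserial: r at 80% | Power at 0.42 | Bivariate normal: r at 80% | Power at 0.42 |
|---|---|---|---|---|
| One-sided | 0.422 | 79.6% | 0.437 | 76.7% |
| Two-sided | 0.468 | 68.7% | 0.485 | 65.7% |

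The Fisher z approximation gives 0.445 one-sided and 0.492 two-sided. The stated 0.42 matches only the one-sided point-biserial cell.

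**4. Could another sample size rescue a two-sided reading?** At n = 35, d = 0.487 and r = 0.44 to 0.46. At n = 60, d = 0.368 and r about 0.35. Neither gives 0.46 and 0.42.

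**5. H2a under FDR.** Counting from Outcome measures: three activity-monitor measures, two CRIS scales, three SF36 subscales and the FAI, so 3 + 2 + 3 + 1 = 9. The article names neither the method nor the family size. Benjamini-Hochberg at 0.05 and independent outcomes are assumed here. The strictest step is 0.05 / 9 = 0.0056. At that alpha, power at f = 0.152 is 50.7% and the detectable f is 0.192. Simulated power per real effect at f = 0.152:

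| Real effects among nine | Power |
|---|---|
| 1 | about 51% |
| 5 | about 68% |
| 9 | about 77% |

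If all nine are real, f of about 0.157 restores 80%.

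**6. H3 under FDR.** The same nine measures, n = 30, each real r = 0.42, bivariate normal, with correlations of 0.3 to 0.5 between measures assumed:

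| Real correlations among nine | Two-sided | One-sided |
|---|---|---|
| 1 | about 33% | about 42% |
| 9 | about 56% | about 70% |

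Unadjusted two-sided power in the same simulation is about 66%.

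**The case against.** The stated figures are coherent under one reading. The article names G*Power 3.1, whose point-biserial model gives r = 0.422 one-sided, and the one-sided paired *t* gives d = 0.465. H1b predicts improvement and H3 a direct correlation, so one-sided tests are defensible, and nothing in the article says two-sided. A reader might infer that d = 0.46 and r = 0.42 are arithmetic errors. The documents do not support that: what they show is an undeclared convention, and the shortfall in steps 2 and 3 depends on two-sided testing. This part of the objection stands. Part of the H3 gap also comes from the choice of correlation model: with point-biserial held fixed, two-sided power is 69% rather than 66%.

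On FDR, the similar-power statement is correct for H2b. The 51% and 33% figures are lone-effect worst cases, and if the intervention improves integration broadly the H2a loss is small. Quoting unadjusted power for secondary outcomes is also common. All of this stands, but it does not remove the point: under the assumptions above, neither H2a nor H3 reaches 80% at the stated effect in any scenario examined, one-sided H3 included.

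Nor does the article say it would read a null H2a as proof of no effect. It says the contrary about association, so the risk lies with readers of the power statement.

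**Conclusion.** The point holds in a limited form.

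- **Sidedness (conditional).** d = 0.46 and r = 0.42 are one-sided, unadjusted values at n = 30, and this is not declared. If the tests are two-sided, the detectable values are d = 0.53 and r about 0.47 to 0.49, and power at the stated effects is about 12 points below 80% for H1b and 11 to 14 points below for H3.
- **FDR (independent of sidedness).** The Aim 2 claim is too favourable for H2a (about 51% to 77% at f = 0.152), and the H3 figure is before correction (about 33% to 56% two-sided). These ranges rest on Benjamini-Hochberg, a family of nine counted from the article, independent outcomes for H2a and the between-measure correlations assumed for H3.

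A reader might go further and infer that the trial is too small or its primary power claim wrong. The documents do not support that: f = 0.152 for H1a reproduces, and the sample size rests on it. FDR does not touch H1b, and H2b keeps its stated power. Severity is minor to moderate.

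**What to change.** In the sample-size paragraph:

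1. Settle sidedness for H1b and H3. Either declare one-sided tests, keeping d = 0.46 and giving r about 0.44 for a bivariate-normal correlation, or restate the figures as two-sided, d = 0.53 and r about 0.49. The Analysis plan should say the same.
2. Limit the similar-power statement to H2b.
3. For H2a, give the range under FDR: detectable f from slightly above 0.152 (about 0.157 if all nine effects are real) up to 0.192 (one real effect). Name the FDR method and the measures in the family.
4. For H3, say that the figure is before FDR or give its range under FDR.

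The cost is a few sentences. No participants are added and the primary analysis is unchanged. If two-sided figures are chosen, the quoted detectable effects become less favourable. The change should be made before results are interpreted.

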### CBPT intervention

Below is a summary of the primary tasks undertaken during each of the eight sessions.
*Session 1*: The initial goal of session 1 is to introduce the participant to the eight-session CBPT intervention and develop rapport. The behavioral therapist will deliver psychoeducation on how the use of the video games can improve balance as well as how balance confidence can impact behavior. Participants’ baseline physical skills on active video games will be assessed using two games (Trash Bin and Italian Alps; see Table 1 for a full description of the games) and the behavioral therapist will introduce the importance of goal setting in behavioral change. The behavioral therapist will introduce the *Behavior Recording Form for Prosthesis Use*, which is a standard behavior record with modifications to assess activity avoidance due to prosthesis concerns. Between-session assignment includes completion of the *Behavior Recording Form for Prosthesis Use* (Additional file 1)*.**Session 2*: Session 2 will begin with a brief participant check-in regarding health and any falls during the prior week to ensure that the participant is safe to continue physical therapy. Next, the participant will be introduced to the four new video games not used during session 1 which will be played during the course of the intervention (Table 1). After completing the video games, the behavioral therapist will review the completed *Behavior Recording Form for Prosthesis Use* with the participant to gain an understanding of the participant’s activity restriction and avoidance behavior. Specific behavioral goals will be developed with the participant. The behavioral therapist will review the *Breathe to Relax* form with the participant, which teaches diaphragmatic breathing for relaxation (Additional file 2)

**Table 1 Tab1:** Description of virtual reality games

Name of game	Description
Trash Bin Game	The player must shift their center of pressure (COP) left or right to move a trash bin to catch falling waste, which only falls vertically. The difficulty of the game can be increased by increasing the rate at which paper falls. The game can be played while shifting COP with feet in place, while side-stepping or while walking by adjusting spatiotemporal gait parameters. A screen capture is shown below
Traffic Jam	The goal of Traffic Jam is to allow cars, moving in two directions, to pass through an intersection, which is blocked when standing on both legs. The intersection clears by unloading one limb and shifting weight over the other limb; if cars are in the right lane then weight must be shifted to the left limb (*left yellow foot print* will disappear) and vice versa to clear the intersection. Traffic Jam focuses on limb loading and unloading and is only played while keeping both flat on the ground. A screen capture is shown below
Playing Soccer	Playing Soccer is initially played while shifting weight side to side and standing in place. Like the Trash Bin Game it can also be played shifting weight by side-stepping or by altering stepping parameters (step length, step width, and stance time) while walking. However, the side-stepping and walking options are not presented until later in the intervention. In all modes of the game, balls are dropped from the sky and fall downwards on the screen and the goal is to continuously bounce the ball off of a paddle, which can be moved by side-to-side shifting of the COP. The ball can ricochet off of side nets. For every ten bounces in a row an additional ball falls. Each gaming mode (standing, side-stepping, or walking) has three levels of difficulty defined by the length of the paddle (decreasing the length of the paddle increases difficulty). A screen capture is shown below
Playing Arkanoid	Playing Arkanoid is first played while standing in place. It can also be played in side-stepping mode or walking mode, but these modes are not shown until later in the intervention. In Playing Arkanoid, a ball is dropped from the sky and falls downwards on the screen. The goal is to continuously bounce the ball off of a paddle so that the ball hits and breaks a series of bricks at the top of the screen; after hitting the bricks the ball again falls down to the paddle. The paddle can be moved by shifting the COP. The ball can bounce off of side walls. A screen capture is shown below
Forest Walk	Forest Walk is played only in walking mode. A forest scene is projected on the treadmill surface and animals and other objects appear and travel with the speed of the treadmill belt; the goal is to make on-line adjustments to the gait pattern in order to avoid stepping on the animals or other objects while intentionally stepping on projected stars and soccer balls; points are awarded for stepping on the proper objects and points are subtracted for stepping on all other objects. The game targets gait adaptability. An overhead view of the treadmill is shown below
Italian Alps	The Italian Alps game is only played in walking mode. In Italian Alps, the player “pushes” a cart through a street and must collect ingredients to make a pizza (see bar across the bottom horizontal bar) to make a pizza while avoiding crashing into other objects such as flower boxes. The motion of the cart tracks the center of pressure (COP) and the flow of the scene is dictated by walking speed. A screen capture is shown below

Between-session assignments will include completion of the *Behavior Recording Form for Prosthesis Use*, reviewing the *Breathe to Relax* form, as well as practice the breathing skill.
*Session 3*: After a brief check in to ensure the participant is well, the participant will play all four video games from Session 2. The behavioral therapist will then conduct an in-depth review of between-session assignments to continue skill building in behavior recording and goal setting. Additionally, the behavioral therapist will review and practice diaphragmatic breathing with the participant as well as refine initial behavioral goals. The behavioral therapist will then introduce systematic exposure to the participant in the context of reducing fear and changing behavior. This will be followed by an exposure exercise. The exposure exercise will be developed through a collaborative process between the behavioral therapist and the physical therapist based on an emerging understanding of the participant’s fear exposure hierarchy and physical ability. A fear exposure hierarchy is composed of a series of gradated tasks based on level of provoked fearfulness. An example of an exposure exercise is asking a participant that avoids reaching for an object above their head to practice reaching up high. Exposures will be conducted in the lab under the guidance of the behavioral therapist as well as at home in between sessions.

Between-session assignments will include completion of the *Behavior Recording Form for Prosthesis Use*, practicing *Breath to Relax*, and an at-home exposure exercise.
*Sessions 4 through 7*: The physical therapist will continue to work on games with the participant. The behavioral therapist will continue to use and review previously introduced procedures, including physical skill acquisition, during physical therapy intervention, behavior recording, diaphragmatic breathing, and community-based exposure exercises.

Between-session assignments continue to include completion of the *Behavior Recording Form for Prosthesis Use*, using the *Breath to Relax* form, and performing an at-home exposure.
*Session 8*: The final session will focus on summarizing the participant’s behavior change goals and progress made towards completing goals, as well as physical progress in the component and any learned behavioral strategies. The behavioral therapist will discuss strategies to continue to further gains as well as strategies for preventing relapse.

#### Key informant interview

At the end of the CBPT intervention (or at drop-out), participants who received the intervention will complete a 30–60 min, recorded, individual interview with investigators to discuss their experience with the intervention. A semi-structured interview will be used to assess the following areas.

#### Intervention experience

Participants will be asked to discuss what they liked and disliked about the intervention, their preference for the length of the intervention and the length of the individual sessions, the reasons they attended or missed sessions, their thoughts on combining the CBT and PT strategies, and the role of the CBT and gaming exercises in addressing their balance confidence and activity restriction. We will also obtain feedback on the CBT forms and assignments, including information on comprehension, burden, and usefulness for addressing balance confidence and activity restriction.

#### Barriers to participation

Participants will be asked about barriers to integration that they felt were not addressed during the intervention, as well as what the intervention could include to address those barriers.

#### Opinions on recruitment

Participants will be asked about advertising messages and recruitment venues that would increase the appeal of participating in similar future studies.

### Training and oversight of behavioral therapist and physical therapist

Two advanced, clinical psychology doctoral students will be trained by two licensed clinical psychologists to deliver the CBT portion of the intervention. The behavioral therapists will review the treatment manual, which will be followed by four 2-h training sessions covering balance confidence, CBT, the integration of CBT into a PT setting, and understanding the psychological and physical health sequelae of a leg amputation. Two training sessions will focus on the delivery of the CBT strategies. This will include a review of CBT theory and specific CBT strategies used to address balance confidence and activity restriction. In addition, behavioral therapists will role-play the delivery of the CBT strategies to ensure intervention fidelity and to provide feedback on adherence of the intervention protocol. Potential problems with the delivery of the CBT content will be discussed (e.g., participant fails to routinely complete assignments).

Once the intervention begins, behavioral therapists will receive supervision by licensed clinical psychologists. Supervisors will listen to audio recordings of the first eight sessions for each behavioral therapist and provide corrective feedback; thereafter, 10% of sessions will be reviewed. The behavioral therapists will also attend weekly supervision meetings to discuss their participant’s progress and ensure fidelity to the intervention. Behavioral therapist and auditor checklists for each session will be used to ensure that treatment objectives for each CBPT session are met. The behavioral therapist will complete the behavioral therapist checklist after each session. A random selection of audio-recorded sessions for each participant will be audited by supervisors to monitor treatment fidelity. They will complete the appropriate auditor checklist. When a session is reviewed with less than 85% of treatment-specific objectives met, supervisors will remediate training as needed. This process will continue through all treatment waves so that drift can be swiftly corrected.

The research teams’ senior licensed physical therapist will train a physical therapist to complete the PT components of the intervention. After reviewing the training manual, the sessions will include training on the operation system used for administering physical therapy exercises and all safety features in the laboratories. The physical therapist will also learn how to recognize adverse events, including excessive exertion, and be taught to monitor and assess vital signs throughout the intervention to avoid excessive exertion. Most importantly, the physical therapist will be instructed on how to regress and progress the level of difficulty for each game following the protocol.

